Of note, different cellular processes are involved in the mechanism of action of radioablation; the therapeutic effect of SBRT is supposed to arise basically from the induction of cellular death and transmural fibrosis that leads to the abolishment of abnormal conduction/automaticity in the myocardial tissue responsible of the arrhythmia [16, 17]. Fibrosis maturation is however progressive and requires several weeks to complete, so that in the intermediate phase, other factors, including acute inflammation and vascular injury, may impact on short-term outcome [16, 18].

Recently, SBRT has been used for the treatment of 35 patients with VT [13, 19–30]. SBRT, guided by imaging techniques partially integrated by electrocardiographic and/or electroanatomical data, significantly reduced in these patients the arrhythmic burden, in the absence of major adverse events correlated with the treatment applied.

Based on these evidences, we designed a spontaneous, prospective, experimental (phase Ib/II), open-label study to validate efficacy and safety of SBRT in a well-defined cohort of patients with recurrent VT not eligible to conventional catheter ablation.

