### Follow-up

Adverse effects will be classified according to the international Common Terminology Criteria for Adverse Events v 5.0/CTCAE document.

A follow-up phone-call will be performed once a week for the first 4 weeks after SBRT.

Regular cardiological follow-up visits, including 12-lead ECG and ICD interrogation, will be performed 3, 6, and 12 months after SBRT. Echocardiography examination and SF-36 health questionnaire will be provided 3, 6, and 12 months after SBRT. Patients will be visited by a radiation oncologist, and thorax CT will be performed 3 and 12 months after SBRT.

Pharmacological therapy, including antiarrhythmic drugs, will be maintained the same as before SBRT during the entire follow-up.

With regard to the early post-SBRT phase and the possible occurrence of transient processes impacting on cardiac arrhythmogenicity, accordingly to literature [16–18, 21], a 6-week “blanking period,” starting immediately after SBRT treatment, will be considered in the analysis of VT recurrences during follow-up.

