### Endpoints of the study

#### Primary endpoints

Two primary endpoints of the study have been defined, represented by safety and efficacy of the treatment, respectively.Primary safety endpoint is to evaluate the safety of radiation therapy in the acute phase (during the first 30 days of the procedure) and at 3, 6, and 12 months. The incidence of serious adverse events related, or presumably related, to radioablation will be assessed as a percentage of the enrolled patients. Serious adverse events were the following:DeathCardio-circulatory arrestAcute myocardial infarctionCardiogenic shockPericarditis, myocarditis, and/or endocarditisAcute heart failureGastro-esophageal lesion (ulcer/stenosis/fistula/hemorrhage/perforation)Bronchopulmonary infectionInjury to the respiratory system (fistula/bronchial or tracheal stenosis, pulmonary fibrosis)Radio-induced oncogenesisPrimary efficacy endpoint is to evaluate the procedural effectiveness of therapy at 3, 6, and 12 months, represented by the total number of VT/VF episodes occurring after “blanking period,” compared with the period preceding the radioablation procedure (6 months).

VT episodes will be categorized as follows:VT episode > 30 s, regardless of the intervention of the ICDVT episode conditioning ICD intervention by means of “anti-tachycardia pacing” electrical therapy (without shock delivery)VT episode conditioning ICD shock intervention

The 6-week “blanking period” will start on the procedure day.

As a rule, pharmacological therapy, including antiarrhythmic drugs, will be maintained the same as before SBRT during the follow-up period. Changes of the pharmacological therapy will be determined only by specific clinical reasons.

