### Analysis of previous experiences

To the best of our knowledge, nine clinical studies are currently underway regarding the use of stereotactic radiation therapy for the treatment of ventricular arrhythmias, registered at clinicaltrials.gov as NCT02919618, NCT02661048, NCT03601832, NCT03819504, NCT03349892 (suspended), NCT04066517, NCT04162171, NCT04065802, and NCT03867747. Results are available and published exclusively for the first two of them.

Some studies in literature already showed that radioablation allows to reduce the occurrence of arrhythmic episodes without significant side effects directly imputable to the treatment and hence demonstrated both its efficacy and safety. Loo and colleagues [20] carried out the first-in-human treatment of ventricular arrhythmia. No acute and late complications were reported, but the efficacy of the treatment was limited to the first months of the treatment. Efficacy and short-term safety were also confirmed in other studies in which only one patient was treated [22, 23, 26–28, 30]. Neuwirth and colleagues [24] reported the second largest case series on the safety and efficacy of SBRT to treat patients with recurrent VT. During 3 months after SBRT, VT burden was reduced by 87.5% and the treatment was well-tolerated; out of the 10 treated patients, only 4 reported nauseas and only 1 presented gradual progression of mitral valve regurgitation. Severe short-term complications were instead observed by Robinson and colleagues [13], in the context of the abovementioned ENCORE-VT trial. As a matter of fact, out of the 19 enrolled patients, VT episodes were reduced in almost all patients with consequent improvement in quality of life, but 2 patients experienced transient heart failure exacerbation and pericarditis, most likely caused by SBRT. Last but not least, in a series of 5 high-risk patients with scar-related VT, the safety profile of SBRT was confirmed to be favorable by Gianni and colleagues [38]; despite good initial results, all patients experienced however clinically significant recurrences over the mid- to late-term. Given these in part contradictory evidences about long-term efficacy and safety, and due to the fact that SBRT has been mainly used as a palliative therapy in patients with short life expectancy, further studies in the field are eventually required.

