### Possible effects of SBRT: Addressing “pros” and “cons”

The benefit supposed to derive from the use of SBRT is represented by the superior efficacy in the control of VT with respect to the conventional percutaneous procedure. This superior efficacy specifically derives from the hypothesis that the SBRT can result in a more appropriate and discrete substrate modification in patients in whom the conventional approach has failed. In a clinical setting, SBRT will be offered as an option in patients who are not eligible to any interventional or surgical approach due to an unacceptably high procedural risk.

Theoretical disadvantages associated with SBRT relate to the fact that we will use a novel therapeutic approach that has been tested only in selected groups of patients; therefore, there is no evidence of its efficacy as a standard treatment. Of note, for STRA-MI-VT patients, this limitation has little significance as all participants will be first categorized as nonresponders or not suitable for any conventional approach. In addition, SBRT may be responsible for cardiac and noncardiac adverse effects, due to the higher radiation exposure of the patients. Even if these effects are, based on the literature, transient, and of mild to moderate entity, specific attention will be given in our study to prospectively evaluate cost-effectiveness of SBRT.

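### The primary safety rate rests on a closed list of diagnoses with no severity threshold, so it can count mild or CT-only findings as serious and leave out severe related events that are not listed

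*Protocol article*

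**What the plan says.** Under Primary endpoints, the safety measure is stated as follows: "The incidence of serious adverse events related, or presumably related, to radioablation will be assessed as a percentage of the enrolled patients". It is assessed over the first 30 days and at 3, 6 and 12 months. The definition comes next, introduced by "Serious adverse events were the following", and consists of ten entries. Some are severe by nature: death, arrest, infarction, shock. Others span a wide range of severity: inflammation of the pericardium or myocardium, bronchopulmonary infection, and damage to "the respiratory system (fistula/bronchial or tracheal stenosis, pulmonary fibrosis"). Radiation-induced cancer is also an entry. No entry has a grade, symptom, hospitalisation or intervention threshold, and none covers other severe events.

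Under Follow-up, a severity system is named: "Adverse effects will be classified according to the international Common Terminology Criteria for Adverse Events v 5.0/CTCAE document". Nothing connects it to the primary endpoint. The same section says that "thorax CT will be performed 3 and 12 months after SBRT", and Table 1 agrees.

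**The concern.** Safety is one of two primary endpoints, and the Conclusions link wider use of the treatment to reaching the primary endpoints and to treating safely. The headline percentage therefore has to mean something definite, and the definition works against that in two directions.

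- **Over-counting.** Pulmonary fibrosis is listed without qualification, and CT looks for it in every patient. A symptomless change in the irradiated field would readily be judged related, so the relatedness condition does not remove it. Mild pericarditis and mild infection enter in the same way.
- **Under-counting.** A severe related event that is not on the list adds nothing to the rate. The article itself raises two candidates under Analysis of previous experiences: progression of mitral regurgitation in one patient of a 10-patient series, and possible damage to the ICD.

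A third, smaller matter is radiation-induced cancer. It is a component of the endpoint, but follow-up ends at 12 months. A zero there would say little about the risk, yet it would sit inside the primary safety result.

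**Working it through.** The article gives no expected rate, threshold or test for the primary safety endpoint, so there is no stated figure to reproduce. The check is of the definition, followed by what one patient is worth.

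**Applying the definition as written**

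| Event, judged related | On the list? | In the primary rate? |
|---|---|---|
| Death | yes | yes |
| Pulmonary fibrosis seen only on scheduled CT | yes, no threshold | yes |
| Mild pericarditis or bronchopulmonary infection | yes, no threshold | yes |
| Severe valve deterioration | no | no |
| ICD damage | no | no |

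The word serious does not filter these rows, because the list is what defines it.

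**Weight of one patient.** Input: 15 planned patients (Methods). 1/15 = 6.7 percentage points.

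**Illustrations, with exact (Clopper-Pearson) 95% intervals.** The event counts are assumptions; the document gives none.

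- Three patients with CT-only fibrosis and no other event: the list rate is 3/15 = 20.0% (4.3% to 48.1%). Counting only grade 3 or higher, it is 0/15 = 0%, with upper limit 1 − 0.025^(1/15) = 21.8%.
- One patient with a severe related event off the list and no other event: the list rate is 0/15 = 0% (0% to 21.8%). If the event counted, it would be 1/15 = 6.7% (0.2% to 31.9%).

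**Range for the over-counting.** Let s be the proportion with a truly severe listed event and q the proportion with CT-only fibrosis, both assumed and treated as independent. The list rate is 1 − (1 − s)(1 − q).

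| s | q = 10% | q = 30% | q = 50% |
|---|---|---|---|
| 5% | 1 − 0.95 × 0.90 = 14.5% | 1 − 0.95 × 0.70 = 33.5% | 1 − 0.95 × 0.50 = 52.5% |
| 10% | 1 − 0.90 × 0.90 = 19% | 1 − 0.90 × 0.70 = 37% | 1 − 0.90 × 0.50 = 55% |

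A rate restricted to severe listed events would stay at s. The table shows the direction and how sensitive the rate is to q; it predicts nothing.

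**How the article labels earlier events.** The Introduction summarises 35 treated patients "in the absence of major adverse events correlated with the treatment applied", and its references include the 19-patient trial. Analysis of previous experiences describes that trial's complications as severe: "2 patients experienced transient heart failure exacerbation and pericarditis, most likely caused by SBRT". The section on pros and cons calls effects in the literature "transient, and of mild to moderate entity". If those two patients' events match the list entries for acute heart failure and pericarditis, which is an inference, the list would give 2/19 = 10.5% (1.3% to 33.1%).

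**The case against.** A fair defence runs as follows.

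- **Operational detail.** An article commonly leaves seriousness and grading criteria to the full protocol. That would answer a complaint about silence. Here, however, the article states the definition, and the definition is a closed list. If the full protocol holds a severity rule, the two should be brought into line.
- **Conservatism.** Counting organ-specific radiation injury at any severity leans towards over-reporting harm, which is defensible in an early-phase trial. This stands, and it is a reason to keep the list. It does not answer the omission of severe unlisted events.
- **Limited consequence.** The endpoint has no pass mark, and the stopping rule uses four unambiguous catastrophic events. Both statements are correct. The flaw affects the estimate and how it is read, and no formal decision turns on it.
- **Other reporting.** A reader might infer that deaths would be hidden among CT findings, or that unlisted toxicity would be lost. The document supports neither. Global mortality is a secondary endpoint in its own right, and adverse effects are evaluated at every stage from treatment onward and classified by CTCAE. An unlisted toxicity that leads to a listed event also enters through that event.
- **Labels.** A reader might take the differing labels for earlier events as a product of the ungraded endpoint. The difference is real, but it lies in background text. The Introduction and the pros-and-cons section name neither pericarditis nor heart failure, and Primary endpoints holds the only operative definition.

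**Conclusion.** The point holds for the headline rate. As defined, the primary safety percentage mixes severities for the entries that are not severe by nature, and it excludes severe related events that are not listed. Each patient affected is worth 6.7 percentage points. How many would be affected cannot be derived from the document; the 3-of-15 example and the values of s and q are illustrative only.

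A reader might go further and conclude that the list should be replaced by all grade 3 or higher events whatever their cause. The document does not support that. Eligible patients have refractory VT and may have an ejection fraction as low as 20%. Without the relatedness condition, the rate would fill with background events and could count VT recurrence, which is the efficacy outcome.

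On radiation-induced cancer, the narrow statement is that 12 months is too short to inform it. Scheduled follow-up imaging includes echocardiography at 3, 6 and 12 months as well as thorax CT, but that does not change the limit set by the duration. The article does not claim that 12 months excludes late cancer.

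**What to change.** Revise the safety paragraph under Primary endpoints:

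1. Keep the condition that events are related or presumed related to radioablation, and keep the present list.
2. Add to the endpoint any other related adverse event of CTCAE v5.0 grade 3 or higher.
3. Report the rate in total and split by grade: patients with at least one grade 3 or higher event, and patients whose only events are grade 1–2 or found on CT alone.
4. State that radiation-induced cancer cannot be assessed within 12 months and that the safety conclusion does not extend to it.

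The cost is small. CTCAE classification is already planned, so no visit or examination is added. The composite becomes slightly broader and the safety table slightly longer. The stopping rule needs no change on this account.

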#### Calculation of the target sample size and statistical analysis

A sample of 15 patients will allow a 60% reduction in ventricular arrhythmic episodes to be assessed as significant (*p* < 0.05), assuming an average of 10 episodes in the 3 months preceding the procedure, with a statistical power of 90%. Continuous variables will be expressed as mean ± standard deviation or median and interquartile range variables with non-normal distribution, and discrete variables as absolute numbers and percentages. Primary efficacy endpoint (reduction of ventricular arrhythmic episodes) and secondary endpoints (clinical, echocardiographic, and psychometric characteristics) will be evaluated with the Student’s *t* test for paired data (continuous variables with normal distribution) or with the Wilcoxon sign rank test (variables with non-normal distribution). Kaplan-Meyer curves will be developed for event-free survival analysis at follow-up. All tests will be two-tailed and a *p* < 0.05 will be considered significant.

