### Study organization and status

Patients are selected from a population submitted to the Centro Cardiologico Monzino (CCM) as nationwide referral center for VT ablation; the SBRT treatment will be carried out at the Istituto Europeo di Oncologia (IEO) that is one of the largest radiotherapy facilities in Italy.

Recruitment started in September 2019 and is expected to end in September 2021. Two years are planned for enrollment as all participants will be selected on the basis of strict inclusion/exclusion criteria being nonresponders to, or not suitable for, any conventional approach. At the date of submission of the manuscript, 4 patients underwent SBRT and 3 completed a 3-month follow-up.

Preliminary results are expected within 1 year from the study beginning; final data analysis will be provided once follow-up period will be completed for all patients (approximately September 2022). On August 26, 2019, the STRA-MI-VT trial was prospectively registered at clinicaltrials.gov (NCT04066517).

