## Conclusions

The existing research confirms that SBRT might represent a relatively effective and well-tolerated therapeutic option in patients with VT who have failed other approaches [37].

STRA-MI-VT study aims at demonstrating that SBRT may represent an alternative therapeutic option in selected patients with substrate-related VT, thanks to a potentially favorable cost-effectiveness ratio. An advanced combined multimodal imaging will be used to characterize the arrhythmogenic substrate and to identify the target for SBRT, thus STRA-MI-VT is supposed to provide significant information to define the adequacy of this novel imaging-integration methodology.

SBRT is widely used in oncology to treat small primary or secondary malignant lesions to high doses in few fractions, leading to local control of about 90% [41]. In the last years, it has been proposed to some benign conditions like trigeminal neuropathy, acoustic neurinomas, or arteriovenous malformations [42]. VT is a condition that might prospectively benefit from this noninvasive approach.

Preliminary results are expected to be available within 1 year. If primary endpoints of STRA-MI-VT will be reached, SBRT has the potential to be offered as a novel therapeutic option to a larger population of patients with mostly intractable VTs, based on the attractive possibility to treat also substrates inaccessible to conventional approaches in a safe and less-invasive manner.

Finally, the methodology of the STRA-MI-VT is based on the cooperation of different teams, with specific competences in arrhythmology, cardiac imaging, and radiation therapy, in an attempt to validate and share a multidisciplinary workflow process that may represent the premise for future clinical experiences in the field.

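### Primary efficacy is assessed at 3, 6 and 12 months, every test at two-sided 0.05, and no time point is named as the one that decides

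*Protocol article*

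**What the plan says.** The Protocol article, Primary endpoints, defines a single efficacy endpoint at three times: the "efficacy endpoint is to evaluate the procedural effectiveness of therapy at 3, 6, and 12 months". The measure is the number of VT/VF episodes after a 6-week blanking period that "will start on the procedure day". All three assessments share one comparator, the 6 months before treatment.

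The section on sample size and statistical analysis evaluates this endpoint with the paired t test or the Wilcoxon signed rank test. One rule covers everything: "All tests will be two-tailed", and p "< 0.05 will be considered significant". The sample size statement gives 15 patients, a 60% reduction from an average of 10 episodes, and 90% power. Its only time reference is the 3 months before the procedure; it names no post-treatment visit.

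The Conclusions make wider use of the treatment depend on the result: "If primary endpoints of STRA-MI-VT will be reached". The article does not say how a split result across the three visits would be read.

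**The concern.** Three comparisons of the primary efficacy measure, each at an unadjusted two-sided 0.05, give three chances of a significant result. With no stated hierarchy, a significant result at one visit could be reported as meeting the endpoint whatever the other two show.

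The visits may well disagree. Under Analysis of previous experiences, the article describes a first treated patient whose benefit was confined to the early months, and a series of 5 patients with good initial results who all had clinically significant recurrences later. The Discussion adds that the effect is expected to appear only after months. After a 6-week blanking period, the 3-month assessment covers only about 1.5 months. Early-only and lasting success are therefore different findings, and the article does not say which one it seeks.

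**Working it through.** **1. The plan's own figure.** A 60% reduction from 10 episodes is a mean difference of 6. Power of the paired t test with n = 15 is P(|T| > t(0.975, 14)), where T is noncentral t with 14 degrees of freedom and noncentrality (6/SD) × √15. The SD of the paired difference is not stated. Solving for 90% gives SD = 6.66 (standardised effect 6/6.66 = 0.90). Power would be 99% at SD 5, 77% at SD 8 and 58% at SD 10. The 90% can be neither confirmed nor refuted, and it is attached to no visit.

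**2. Upper limits for three tests at 0.05, no true effect.**
- Independent tests: 1 − 0.95³ = 0.143. Bonferroni limit: 3 × 0.05 = 0.15.
- Benefit direction only, independent: 1 − 0.975³ = 0.073, against 0.025.

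**3. Correlated tests.** The three tests share a baseline, so they are positively correlated. The correlation is not stated and is assumed here. Simulation of three paired t tests, n = 15, 200,000 runs:

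| Common correlation | At least one p < 0.05 | At least one false benefit |
|---|---|---|
| 0 | 14.2% | 7.4% |
| 0.5 | 12.7% | 6.4% |
| 0.7 | 11.2% | 5.6% |
| 0.8 | 10.1% | 5.0% |
| 0.9 | 8.5% | 4.3% |
| 0.95 | 7.5% | 3.8% |

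**4. Correlation implied by the design.** Take episode rates with a 6-month baseline and post-blanking windows of length L (in months). With unit within-patient variance per month and between-patient variance v in the true change, cov(i, j) = v + 1/6 + overlap/(Lᵢ × Lⱼ).
- Cumulative windows have lengths 3 − 1.5 = 1.5, 6 − 1.5 = 4.5 and 12 − 1.5 = 10.5. With v = 0 the variances are 0.833, 0.389 and 0.262. The correlations are √(0.389/0.833) = 0.68 (3 and 6 months), √(0.262/0.833) = 0.56 (3 and 12) and √(0.262/0.389) = 0.82 (6 and 12). With v from 0 to 1, the chance of at least one p < 0.05 is 11.1% down to 8.7%, and of a false benefit 5.6% down to 4.4%.
- Separate windows (1.5 to 3, 3 to 6 and 6 to 12 months): 13.5% down to 10.5%, and 6.8% down to 5.3%.

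A further null simulation of paired t tests on rates gave 8% to 10% in either direction and 3% to 5% for benefit.

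**5. Sensitivity to skewed counts.** With strongly overdispersed counts and cumulative windows, the any-of-three rate rose to 12.4% (t) and 18.2% (Wilcoxon). In those runs the 3-month test alone already rejected in 7.0% and about 11%. Part of the excess is therefore a single test missing its level, not multiplicity, and it is not counted here.

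**6. Ratios.** 7.5/5 = 1.5 and 14.3/5 = 2.9. For benefit, 3.8/2.5 = 1.5 and 7.3/2.5 = 2.9.

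**The case against.** The strongest objection is that the article nowhere says one significant visit is enough. It speaks of one primary efficacy endpoint, and a rule requiring all three visits would not inflate the error. This stands, and it makes the inflation conditional. What remains is that the article states neither rule, so a split result has no prespecified reading.

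A second objection is that a testing order usually belongs in the analysis plan, which is not shown. That would excuse silence alone. Here the article itself fixes three primary time points and a flat threshold for every test. If the analysis plan already names a deciding visit, citing it settles the matter.

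Third, this is a single-arm phase Ib/II study of 15 patients. That limits the weight of the point but does not remove it, because the Conclusions tie wider use to the endpoints being met.

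Three stronger readings are tempting but not supported:
- The plural in "If primary endpoints of STRA-MI-VT will be reached" might be taken to mean any of the three visits. The Primary endpoints section defines two primary endpoints, safety and efficacy, and the plural refers to those.
- "Preliminary results are expected within 1 year from the study beginning" might be read as a further test of efficacy. The article mentions no interim efficacy test, and it places the final analysis after all follow-up is complete.
- Raw episode counts would show far more false rejections. That comes mainly from comparing windows of about 1.5, 4.5 and 10.5 months with a 6-month baseline, and most of it appears with a single test. It is a separate issue.

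**Conclusion.** The point holds in conditional form. The article fixes three primary efficacy assessments and an unadjusted two-sided 0.05 without saying which assessment decides. If any one may count as success, the false-positive rate is about 8% to 14% in either direction. For a false claim of benefit, the error a sponsor could act on, it is about 3% to 7% against 2.5%.

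The size rests on three assumptions: that each visit gets its own test, which is the natural reading of the two sections together but is not spelled out; that each test on its own holds its level; and an assumed correlation. Cumulative counts with a shared baseline put the inflation near double. The change is worth making, but the point does not by itself invalidate the design.

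**What to change.** Before the final analysis, name one time point as the deciding primary efficacy comparison and state why. The choice is the sponsor's, and 6 and 12 months are both defensible. Matching the 6-month baseline is not a decisive reason for 6 months, because the post-blanking window to month 6 is only about 4.5 months. Then either test the other two in a stated order, each at 0.05 only if the one before is significant, or report them as supportive.

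Disclose the timing of the choice. When the article was submitted, 4 patients of this open-label study had been treated and 3 had completed 3 months of follow-up.

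The cost is a few sentences and that disclosure. The deciding test keeps its full 0.05, so the type I error is 5% and the planned power at 15 patients is unchanged. Success at a non-deciding visit alone can no longer be claimed.

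The alternative, three equal tests at 0.05/3, is dearer. At the back-solved SD of 6.66, power per test falls from 90% to 76.8%, and 20 patients would be needed to restore it.

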#### Secondary endpoint

Secondary endpoints are the following:Global mortality during follow-up (up to 12 months)Variations in the quality of life of patients in the follow-up (up to 12 months) with respect to the basal conditionChanges in cardiac function assessed by estimating the ejection fraction of the left ventricle on the echocardiographic examination in the follow-up (up to 12 months)

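### The primary efficacy endpoint is a raw episode total with no time-at-risk denominator, so follow-up cut short by death can look like a reduction in VT.

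*Protocol article*

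**What the plan says.** Under Primary endpoints, the protocol article sets out to "evaluate the procedural effectiveness of therapy at 3, 6, and 12 months", and the measure is "represented by the total number of VT/VF episodes occurring after" the blanking period, "compared with the period preceding the radioablation procedure (6 months"). Blanking lasts six weeks from the day of the procedure. No rate, exposure time or death component is part of this definition.

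The section on sample size and statistical analysis tests the change with a paired t test, or a Wilcoxon signed-rank test if the data are not normal. It states that "A sample of 15 patients will allow a 60% reduction in ventricular arrhythmic episodes to be assessed as significant", assuming an average of 10 episodes in the 3 months before treatment.

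Death is handled elsewhere:
- It heads the list of serious adverse events in the primary safety endpoint, but there "The incidence of serious adverse events related, or presumably related, to radioablation will be assessed as a percentage of the enrolled patients".
- All-cause death is a secondary endpoint: "Global mortality during follow-up (up to 12 months").
- Death within 30 days counts towards the stopping rule for the first 5 patients.
- Kaplan-Meier curves for event-free survival are planned, without a definition of the event.

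**The concern.** A count depends on how long one counts. Because the efficacy measure is a total, anything that shortens observation after treatment lowers it, whether or not SBRT works. Death is the most important such cause. The eligibility criteria admit patients with refractory or incessant VT, ejection fraction down to 20%, and severe heart disease or comorbidity that rules out ablation, so some deaths within 12 months are plausible, although no rate is given.

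A death judged unrelated to SBRT does not enter the primary safety endpoint, yet if that patient stays in the paired test it can lower the primary efficacy count. In an uncontrolled study of 15 patients no comparison arm would absorb this. The same missing denominator also makes the three time points incomparable with the baseline for patients who survive.

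**Working it through.** **The plan's own figure.** A 60% reduction from 10 episodes is a paired difference of 6. The article states no SD of that difference, so 15 patients cannot be reproduced, only back-solved: 90% power at two-sided 0.05 with n = 15 requires an SD of about 6.7 (noncentral t; normal approximation 6 × √15 / (1.960 + 1.282) = 7.2). The point here does not depend on this.

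**Inputs.** From the article: 10 episodes per 3 months, a 6-month baseline, 6 weeks of blanking, assessments at 3, 6 and 12 months, 15 patients. My assumptions: months read as 13, 26 and 52 weeks; the planning rate holds through the 6-month baseline; counts run from the end of blanking to each time point; no treatment effect; patients who die are kept with their observed count.

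- Weekly rate = 10/13 = 0.769
- Baseline count = 0.769 × 26 = 20
- Countable episodes for a death in week t = 0.769 × max(0, t − 6)

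**One patient who dies, against 20 at baseline**

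| Death in week | Countable weeks | Episodes | Apparent change |
|---|---|---|---|
| 6 or earlier | 0 | 0 | -100% |
| 8 | 2 | 1.5 | -92% |
| 13 | 7 | 5.4 | -73% |
| 16.4 | 10.4 | 8.0 | -60% |
| 26 | 20 | 15.4 | -23% |
| 32 | 26 | 20.0 | 0% |

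**A patient who survives, also with no effect**

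| Time point | Countable weeks | Episodes | Apparent change |
|---|---|---|---|
| 3 months | 13 − 6 = 7 | 5.4 | 7/26 − 1 = -73% |
| 6 months | 26 − 6 = 20 | 15.4 | 20/26 − 1 = -23% |
| 12 months | 52 − 6 = 46 | 35.4 | 46/26 − 1 = +77% |

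**Cohort total, three of 15 dying by week 6 (baseline 15 × 20 = 300)**
- 3 months: 12 × 5.38 = 64.6, or -78%, against -73% with no deaths.
- 6 months: 12 × 15.38 = 184.6, or -38%, against -23%.
- 12 months: 12 × 35.38 = 424.6, or +42%, against +77%.

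Early deaths push the total down at every time point, on top of the distortion from unequal windows.

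**With a rate.** For survivors, 5.38/7 = 15.38/20 = 35.38/46 = 20/26 = 0.769 per week, so the apparent change is 0% at all three time points. For a death after week 6 the expected rate is likewise 0.769. For a death by week 6 it is 0/0, undefined.

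**Effect on the test.** A simulation with no effect used n = 15, 3,000 runs, gamma-Poisson counts with shape 1, and a constant hazard of death unrelated to VT rate. The baseline was scaled to the 46-week window to isolate deaths. Patients who died were kept with their observed counts in the plain-count analysis; in the rate analysis, those who died during blanking were left out. The table shows falsely significant reductions (nominal 2.5% in that direction).

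| Assumed 12-month mortality | Plain count, t / Wilcoxon | Rate, t / Wilcoxon |
|---|---|---|
| 0% | 2.2% / 2.1% | 2.3% / 2.2% |
| 10% | 3.6% / 4.7% | 2.1% / 2.4% |
| 20% | 7.9% / 10.5% | 2.4% / 2.7% |
| 30% | 15.1% / 17.9% | 2.1% / 2.5% |

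**The case against.** The best defence is that the article does not say how a patient who dies enters the paired test. A reader might infer that such a patient is scored as a treatment success. The document does not support that: it defines no responder or success category, and it states neither that deaths are kept with their observed count, set to zero, nor left out. A handling rule may stand in the full protocol or analysis plan, so its absence from a condensed article is not a fault. This stands, and it limits the point to what the article does state: a total with no denominator.

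For the same reason the point does not extend to quality of life and ejection fraction. The article says only that "secondary endpoints (clinical, echocardiographic, and psychometric characteristics) will be evaluated" with the same paired tests. Whether those become survivor-only comparisons depends on a rule that is not shown.

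It is also fair that deaths are reported in other endpoints and would be visible in 15 patients; that NYHA IV, cardiogenic shock and comorbidity with a prognosis under 12 months are excluded; and that naming death as an endpoint implies no rate.

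A reader might further infer that three deaths of 15 yield a false reduction of 10% (mid-window) or 20% (by the end of blanking) at 12 months. Those figures require scaling the baseline to 46 weeks, which the article does not describe. On the raw count, three mid-window deaths (week 29, 17.7 episodes each) give (12 × 35.38 + 3 × 17.69)/300 = 1.59, or +59%, and three by the end of blanking give +42%. At 12 months the long window outweighs the deaths.

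None of this rescues the total as a measure. It shows that the error can run in either direction, which is itself a reason for a rate.

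**Conclusion.** The point holds in limited form. As stated, the primary efficacy endpoint confounds the frequency of VT with the length of observation. A patient kept in the analysis who dies before about week 32 shows fewer episodes than at baseline with no treatment effect: -100% by week 6, -73% at week 13, -60% at about week 16. Survivors show about -73%, -23% and +77% at 3, 6 and 12 months for the same reason. These figures rest on a constant planning rate and on cumulative counting from the end of blanking.

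The net bias from deaths cannot be fixed from the article, because it gives no mortality. Under assumed 12-month mortality of 10% to 30%, a scaled baseline and deaths kept in, false favourable significance rises from about 2% to about 4% to 18%, and stays at about 2% to 3% with rates.

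**What to change.** Define the endpoint, and the quantity in the paired test, as VT/VF episodes per monitored month. After treatment, count from the end of blanking to the earliest of death, transplant, device removal or the time point; before treatment, use the rate over the six-month baseline.

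A rate alone does not settle deaths during blanking, which have no time at risk. State that these patients are not counted as zero episodes, and print the number of deaths, with those during blanking shown separately, beside each efficacy estimate. Add a sensitivity analysis that treats death as unfavourable, either as a composite or by worst rank.

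Worst rank should not be the mandated primary analysis. It changes the estimand and is costly at this size: with 15 patients, two worst-ranked deaths give a signed-rank statistic of 15 + 14 = 29 and an exact two-sided p of 0.083 even if every survivor improves; three give 42 and p = 0.33.

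The cost is a change of wording before analysis, a little more analysis work, and possibly a less favourable estimate at 3 and 6 months, where the short windows now favour SBRT.
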